### Ada Assessment by Study HCP (Stage 1)

After the recruitment process, the patients will consult with a study HCP, who is a mid-level HCP and will not be involved in the patient’s care. The study HCP will assess the patient using the prototype DDSS and create a differential diagnosis list. Depending on the patient allocation, there will be a difference in the synthesis of the final differential diagnosis list in the assessment (Figure 3): In arm 1, the study HCP will submit a preliminary list before seeing the prototype DDSS’s condition suggestion list. Once the preliminary list is submitted, the study HCP cannot change it. After being able to review the preliminary list and the prototype DDSS’s condition suggestion list, the study HCP will pick his or her top 5 differential diagnoses from both lists and submit a final differential diagnosis list. Conversely, in arm 2, the study HCP will see the prototype DDSS’s condition suggestion list before submitting a final differential diagnosis list. This will give the study HCP the opportunity to consider differential diagnoses from the prototype DDSS and add their own differential diagnoses to create a final differential diagnosis list. The degree to which these lists match the gold standard diagnoses will be judged in a later step by an unbiased physician panel, after the completion of patient recruitment and study data recording.

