**Figure 4 figure4:**
[figure not shown]
Data flowchart. DDL: differential diagnosis list; DDSS: diagnostic decision support system.

The physician panel in step 4 that makes the differential diagnoses will be made up of 3 local physicians, each with at least 3 years of full-time clinical experience (the majority in general medicine), who will carry out a review process; this process will yield the gold standard differential diagnosis list for each case. The physician panel members have been thoroughly screened and chosen by the principal investigator of this study, who is a native Tanzanian doctor with over 20 years of experience as a medical doctor and several additional years of experience as an instructor at Muhimbili University of Health and Allied Sciences. All physician panelists are required to have an active medical license and to be available for at least 9 hours per week during the physician panel process in order to be immersed enough in the process. Two independent “reviewer” physicians on the panel will review the diagnoses from the usual HCP and the study-provided physician, the pseudo-anonymized medical history, and the symptoms of each patient. They will assign a preliminary differential diagnosis list and a principal diagnosis to each case based on history and symptoms alone and then assign a final differential diagnosis list and principal diagnosis based on the full patient clinical file (this will include vital signs and results from medical examinations and diagnostic tests). In case of disagreement between the 2 differential diagnosis lists, a third reviewer will make a final decision. The tenth revision of the International Statistical Classification of Diseases and Related Health Problems will be used to determine all diagnoses.

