The matching of conditions by the physician panel in step 5 will involve matching the diagnoses made by the usual HCP and study-provided physician with the diagnoses made by the reviewer physicians on the physician panel. The same procedure for the DDSS condition list will be carried out by the reviewer physicians. As in step 4, a third reviewer physician will make a final decision if there is disagreement between the 2 reviewer physicians. The primary comparator of the Ada assessment is the differential diagnosis obtained before the addition of vital sign measurement, physical examination, and additional diagnostic tests. Looking at the differential diagnosis list at each point in the patient’s clinical journey is still a relevant point of comparison.

Finally, the data collection performed in these 5 steps will be analyzed (details are in the “Data Analysis” section). In order to determine the usability, usefulness, and acceptability of the prototype DDSS, the usual HCP questionnaires, in addition to the patient questionnaires, will be analyzed and described using methods appropriate to modified Likert-scale questionnaire data [26].

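### The reviewers who write the reference list also read two of the three diagnosis sources and later score all three, with no stated order, so the DDSS comparison with practitioners can lean towards the practitioners

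*Protocol article*

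**What the plan says.** All of this is in the protocol article, Methods.

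- **Step 4, writing the reference (Measurement Methods, text after Figure 4).** Two of the three panel physicians act as reviewers, and the third settles disagreements. The text says that these two "will review the diagnoses from the usual HCP and the study-provided physician", along with a de-identified history and the symptom record. The next sentence says "They will assign a preliminary differential diagnosis list and a principal diagnosis to each case based on history and symptoms alone". A final list follows, based on the full clinical file. Of the whole process the article says "this process will yield the gold standard differential diagnosis list for each case".
- **Step 5, matching (same section).** The task is "matching the diagnoses made by the usual HCP and study-provided physician with the diagnoses made by the reviewer physicians on the physician panel". Then: "The same procedure for the DDSS condition list will be carried out by the reviewer physicians". Also: "As in step 4, a third reviewer physician will make a final decision if there is disagreement between the 2 reviewer physicians". The section adds that the main comparator for the tool is the differential reached before vital signs, examination and tests.
- **Ada Assessment by Study HCP (Stage 1).** The agreement of the study HCP's lists with the reference "will be judged in a later step by an unbiased physician panel".
- **Strengths and Limitations of the Current Study.** The panel and its voting method are presented as giving a highly objective and independent gold standard.
- **Data Analysis.** The proportions correct for the DDSS, the usual HCPs and the study physicians are compared by a chi-squared test, followed if significant by pairwise two-sided Fisher tests of the DDSS against the practitioners.

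**The concern.** Two things are fixed in the text, and a masking sentence in a fuller document would not cure either. First, the diagnoses of two of the compared sources are inputs to the people who write the reference. Second, the same people later decide whether those diagnoses match it. The DDSS list is not named as an input in step 4, so the prior exposure is one-sided.

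A reviewer who has read a plausible diagnosis is more likely to put it in the reference, and more likely to accept it later as a match. Either effect raises the practitioners' score relative to the tool. This bears on the first primary endpoint, where DDSS accuracy is reported alongside that of the usual HCP, and on the planned tests. Outcomes and Outcome Measures says that the pilot is to enable power calculations for a later randomised trial, so a distorted difference would carry into that design.

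**Working it through.** The document states no figure that depends on this point, so there is none to reproduce. The check is a trace of who sees and scores what, followed by an illustration of what a bias would do.

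**1. Exposure by source, as written**

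| Source | Named as read in step 4 | Named as matched in step 5 | Used in |
|---|---|---|---|
| Usual HCP | yes | yes | Endpoint 1; chi-squared/Fisher |
| Study physician | yes | yes | chi-squared/Fisher |
| DDSS list | no | yes | Endpoint 1; chi-squared/Fisher |
| Study HCP lists (preliminary, final) | no | not named there; Stage 1 says the panel judges them | Endpoints 2 and 3 |

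The asymmetry lies between the first two rows and the third.

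**2. The two adjoining sentences in step 4.** One says the reviewers "will review the diagnoses from the usual HCP and the study-provided physician". The next rests the preliminary list on history and symptoms alone. Both hold only if the practitioners' diagnoses are shown after the preliminary list is fixed, and no such order is given. The order matters because the section on Stage 3 places the study physician's consultation after laboratory and diagnostic procedures. A reviewer who had already read that diagnosis would be carrying later information into a list meant to exclude it.

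**3. Are they the same people?** Step 5 twice refers to the reviewer physicians and handles disagreement as in step 4. No second panel is described, so the natural reading is that they are.

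**4. Illustration only.** Assumptions: n = 50 ratings per source (the minimum enrolment), treated as independent; true accuracy p equal in both sources; the practitioner's match rate raised by d; two-sided alpha 0.05. None of p, d or alpha comes from the document.

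Rejection rate = sum over i, j of Bin(i; 50, p) × Bin(j; 50, p + d) × 1[Fisher p-value for i/50 v j/50 ≤ 0.05].

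| d (points) | p = 50% | p = 60% | p = 70% |
|---|---|---|---|
| 0 | 3.5% | 3.2% | 3.1% |
| 5 | 5.8% | 5.4% | 5.8% |
| 10 | 13.4% | 13.2% | 15.5% |
| 15 | 27.1% | 28.7% | 35.4% |
| 20 | 46.3% | 51.5% | 64.0% |

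A normal-approximation cross-check gives 7.2-8.0%, 16.9-20.9%, 32.7-43.4% and 53.3-71.1% for d = 5, 10, 15 and 20. These are higher, as expected, because Fisher's test is conservative. The table ignores the plan's requirement that the chi-squared test be significant first, which can only lower these rates, and it ignores the pairing of ratings within patients.

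**The case against.** The strongest reply is that the article does not say the matchers know where a list came from. It names what is matched to what; labels, format and order are operational details that an article may leave to a fuller protocol. **This stands.** A reader might infer from the separate sentences on practitioners and DDSS that the source is known at matching. The text is silent on that, and applying one procedure to both could equally mean uniform handling.

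Second, the sentence calling the panel unbiased concerns the study HCP's lists, which are not named as step 4 material. **This also stands.** Reading that sentence as contradicted by the reviewers' exposure to other practitioners' diagnoses joins two different sets of lists. The claim in tension with the procedure is the one about objectivity and independence under Strengths and Limitations.

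Third, the preliminary list rests on history and symptoms alone, and the main comparator is the differential before examination and tests. If the practitioners' diagnoses were withheld until the final list, the effect on the reference would be confined to that list. **This stands in part.** The preceding sentence leaves the order open, and even then the same physicians would have read those diagnoses before matching them.

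Fourth, two independent reviewers, a third for disagreements, ICD-10 diagnoses and a pre-existing definition of accuracy limit how free the judgement is. They do limit it, but the provision for disagreement at matching shows that judgement remains, and all the reviewers share the same exposure.

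Last, the anonymisation promised under Data Analysis covers the usual HCPs' ratings. It does not say that matchers cannot tell a tool's list from a practitioner's.

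**Conclusion.** The point holds for the first primary endpoint and for the chi-squared and Fisher comparison of the DDSS with the practitioners. The step 4 wording leaves open whether the reference was written with the practitioners' diagnoses in view, and the same reviewers then score those diagnoses and the tool's list. As written, the likely lean from prior reading is towards the practitioners.

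It should not be extended to all three endpoints on the same footing. For the second and third, which use the study HCP's lists, the only concern is that reviewers might know the arm or the type of list at matching, and the article does not say whether they do.

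The size of the bias cannot be derived from the document. The illustration shows only that the consequence depends on it: slight at 5 points, material from about 10 points at 50 ratings per source. The article says the pilot is not powered to settle its hypotheses, so the greater harm is to the estimate passed on to the later trial. The point rests on the step 5 reviewers being those of step 4, which the wording supports.

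**What to change.** 1. **Step 4.** State that the preliminary reference list is written and locked from history and symptoms before the reviewers see any practitioner's diagnosis. Lock the final list before matching starts.
2. **Step 5.** Give the same reviewers all lists for a case (DDSS, usual HCP, study physician, study HCP preliminary and final) without source or arm labels, in one format and random order, and have them scored in one pass. Name the study HCP's lists in this step, since Stage 1 says the panel judges them.
3. **Strengths and Limitations.** Soften the claim of objectivity and independence, and state that masking is partial.

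The cost is a scripted export from the electronic data capture system and some work on sequencing. No extra reviewers are needed. Matching is planned after recruitment and data recording are complete, so no patient procedure changes.

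Neither step suffices alone. Removing labels cannot undo what reviewers have already read, so the order in step 4 has to be fixed as well. Even with both, reviewers may recognise diagnoses they saw for the final list or guess a source from its wording. Matchers who did not write the reference would remove recognition from prior reading, but would need additional staff.

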**Figure 2 figure2:**
[figure not shown]
The patient journey in the study. Step 1: using the study tool, a differential diagnosis list is created by the study health care practitioner (clinical officer or assistant medical officer). Step 2: using a structured electronic case report form (eCRF), the patient consults with the usual health care practitioner for the determination of a diagnosis. Step 3: using a structured eCRF, the patient consults with a study physician to confirm the findings in step 2 with higher objectivity and a gold standard diagnosis. DDL: differential diagnosis list; pDDSS: prototype diagnostic decision support system.

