### Endpoints

#### Primary Endpoints

The first endpoint will be the condition suggestion accuracy and comprehensiveness of the prototype DDSS, evaluated against the gold standard differential diagnosis determined by the review panel, reported in the context of the accuracy of the usual HCP. The second endpoint will be the study HCP’s condition suggestion accuracy and comprehensiveness, which will be compared between arm 1 (in which the HCPs determine their own list of condition suggestions before seeing the prototype DDSS’s condition suggestions, then create a final ranked list of condition suggestions) and arm 2 (in which they see the prototype DDSS’s condition suggestions before determining their list of overall ranked condition suggestions). The third endpoint will be a comparison of the study HCP's condition suggestion accuracy and comprehensiveness in arm 1 in the preliminary and final DDLs.

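### The reference list for the first primary endpoint is inconsistent: Measurement Methods makes the pre-test differential primary, while the endpoint text uses a panel gold standard that appears to be the full-file list

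*Protocol article*

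**What the plan says.** Under Measurement Methods, two panel physicians work through each case in two passes. First, "They will assign a preliminary differential diagnosis list and a principal diagnosis to each case based on history and symptoms alone"; they "then assign a final differential diagnosis list and principal diagnosis based on the full patient clinical file", which adds vital signs, examinations and tests. A third settles disagreements. The output is described in the singular: "this process will yield the gold standard differential diagnosis list for each case".

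The matching step in the same section then says: "The primary comparator of the Ada assessment is the differential diagnosis obtained before the addition of vital sign measurement", followed by physical examination and further tests. The next sentence keeps the "differential diagnosis list at each point in the patient"'s course as a relevant comparison too.

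Primary Endpoints states that DDSS accuracy and comprehensiveness will be "evaluated against the gold standard differential diagnosis determined by the review panel". Data Analysis likewise scores the top-1, top-3 and top-5 suggestions against the gold standard. Neither section says whether this is the preliminary or the final list. The Stage 1 section uses the same term for judging the lists made in both arms.

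The Stage 3 section places the study physician's consultation after laboratory and diagnostic procedures and presents it as a contribution to the gold standard.

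**The concern.** A diagnostic accuracy figure has meaning only relative to a named reference. Here the matching step points to a differential formed before examination and testing, while the endpoint and analysis text points to a gold standard that appears to rest on everything known about the patient. These are different targets. Against the history-only list, a suggestion later refuted by tests can count as a hit, and a study physician's correct test-driven diagnosis can count as a miss. The choice could therefore move both the DDSS figure and its contrast with the practitioners.

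Three list depths and two measures already give 3 x 2 = 6 headline figures for the DDSS. An open reference doubles that to 12 and leaves the choice to be made after the results are seen. Outcomes and Outcome Measures intends the pilot to supply inputs for later power calculations, so the estimate needs a fixed meaning even though no hypothesis test is powered.

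A second question is whether the history-only list is what its name says, since the panel members who write it are also given the practitioners' diagnoses.

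**Working it through.** The plan states no figure to reproduce: the minimum of 50 is declared pragmatic and no power is claimed. The check is mainly a comparison of texts.

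**Step 1: which list is the reference?**

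| Section | What it says | List it points to |
|---|---|---|
| Measurement Methods, panel step | Two lists; one gold standard results | Final, by implication: it is where the process ends |
| Stage 3 | Post-test consultation feeds the gold standard | Final, by implication |
| Measurement Methods, matching step | Primary comparator is the differential before vital signs, examination and tests | Preliminary: the dividing line is the one between the two panel lists |
| Primary Endpoints; Data Analysis | Scored against the gold standard | Not specified; final if read with the first two rows |
| Stage 1 | Both arms' lists matched to the gold standard | Not specified; affects endpoints two and three |

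No section reconciles the third row with the others.

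**Step 2: is the history-only list free of test information?** The panel step has the two physicians review the usual practitioner's and the study physician's diagnoses together with the history and symptoms. The study physician's diagnosis follows testing (Stage 3). The text does not say that these diagnoses are held back until the preliminary list is written. Test information can therefore reach that list, and so can the answers of practitioners who are later scored against it.

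**Step 3: how much could the choice matter?** None of the following inputs is in the documents except n = 50.

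- q = share of cases in which the two panel lists differ (assumed 10% to 40%)
- c = DDSS hit rate where they agree (assumed 0.70)
- hA, hB = DDSS hit rate in differing cases against the preliminary and the final list

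Accuracy = (1 - q) x c + q x h, so the shift is q x (hA - hB) and cannot exceed q.

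| q | hA | hB | Against preliminary | Against final | Shift (points) |
|---|---|---|---|---|---|
| any | 0.70 | 0.70 | 70% | 70% | 0 |
| 10% | 0.70 | 0.35 | 70% | 66.5% | 3.5 |
| 20% | 0.70 | 0.35 | 70% | 63% | 7 |
| 40% | 0.70 | 0.35 | 70% | 56% | 14 |
| 20% | 0.70 | 0 | 70% | 56% | 14 |
| 40% | 0.70 | 0 | 70% | 42% | 28 |
| 20% | 0.35 | 0.70 | 63% | 70% | -7 |

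For scale, the 95% half-width at n = 50 is 1.96 x sqrt(0.70 x 0.30 / 50) = 0.127 at 70% accuracy and 1.96 x sqrt(0.50 x 0.50 / 50) = 0.139 at 50%. The shift reaches 12.7 points when q is about 0.127 / 0.70 = 18% with hB = 0, or 0.127 / 0.35 = 36% with hB = 0.35. Both scorings use the same patients, so the shift is a difference in definition, not sampling noise, and a larger sample would not remove it.

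**The case against.** The strongest reply is that a reference standard and a comparator are different things. Primary Endpoints names both: the DDSS is judged against the panel and reported in the context of the usual practitioner's accuracy. In Stage 2 the usual practitioner fills in the electronic form during the consultation, and vital signs and test requests come afterwards. The primary comparator could then be the usual practitioner's entry, with no conflict over the reference. This reading fits only in part. Stage 2 does not place the physical examination, and it does not describe the entry as a differential obtained before that examination. The disputed sentence also sits in the panel's matching step and repeats the panel's own division of information. That a second reading is possible adds to the uncertainty.

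The data flowchart (Figure 4) is not visible, and the full protocol may settle the matter. However, the point here is not an omitted detail: the article does state a reference, in sections that do not agree.

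Other parts of the reply stand. A reader might infer that the article calls two different lists the primary yardstick outright. It does not: no sentence equates the gold standard with the full-file list. A reader might also infer that DDSS accuracy will be overstated by a known amount. The documents give no rate at which the lists differ, and the shift could be zero or reversed. The Figure 2 caption, which links the study physician to confirming findings "with higher objectivity and a gold standard diagnosis", might be taken for a third reference. It is better read as loose wording, since the abstract, the panel description and Primary Endpoints all assign the gold standard to the panel. Finally, a history-based target is defensible for a tool that works from questions about symptoms, so the defect is the unsettled choice and not either list in itself.

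**Conclusion.** The concern holds in this form: the reference for the first primary endpoint is inconsistent across the article, and through the shared term the inconsistency extends to the two endpoints on the study practitioners' lists. That the gold standard means the final list is an inference from the panel and Stage 3 descriptions. Separately, as described, the history-only list may carry test information and may not be independent of the practitioners scored against it. The text leaves this open and does not show that it will occur.

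The size and direction of any effect on accuracy cannot be derived from the documents. Under the assumed inputs the choice of list shifts DDSS accuracy by anything from nothing to about the 13-point half-width at n = 50. It goes beyond that only where the lists differ often and the DDSS seldom matches the final one, and the sign can reverse. Because the pilot claims no power, what is at stake is the meaning of the primary estimate and its later use in planning. It should be fixed, but it does not invalidate the study.

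**What to change.** Before matching begins, name one panel list as the primary reference for all three endpoints, in the same words in Measurement Methods, Primary Endpoints and Data Analysis. The final full-file list is the choice that fits the panel and Stage 3 descriptions. Report the DDSS, usual practitioner and study physician results against the other panel list as a labelled secondary analysis.

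Withhold the usual practitioner's and study physician's diagnoses from the panel until the history-only list is locked. This protects that list only; the final list would still draw on those diagnoses by design.

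Do not present the panel's preliminary list, scored against its own final list, as an independent benchmark. The same physicians write both, so the result would partly measure self-agreement.

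The cost is a small change to the panel procedure and one extra set of matched results. Both lists are already collected, and matching comes after recruitment. The stated DDSS accuracy may turn out somewhat lower.
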